### Data Collection Procedures

#### Overview

The parameters assessed at each participant visit, from screening through the 6-month study duration, are summarized in Table 1. Data will be collected through various questionnaires and standardized procedures. All questionnaires used are freely and publicly accessible.

**Table 1 table1:** Summary of parameters assessed during participant visits.

Variables			Screening		Month 0		Month 3		Month 6
**Anthropometric data**									
	Weight	✓		✓		✓		✓	
	Height	✓		✓		✓		✓	
	BMI	✓		✓		✓		✓	
	Triceps skinfold	✓		✓		✓		✓	
	MAMC^a^	✓		✓		✓		✓	
	Body composition	✓		✓		✓		✓	
**Biochemical data**									
	Renal function test	✓		✓		✓		✓	
	Lipid profile	✓		✓		✓		✓	
	Blood glucose profile	✓		✓		✓		✓	
	Dialysis adequacy (kt/V)	✓		✓		✓		✓	
	nPCR^b^	✓		✓		✓		✓	
	Inflammatory markers			✓		✓		✓	
**Clinical data**									
	MIS^c^ score	✓		✓		✓		✓	
**Dietary assessment**									
	Food records	✓		✓		✓		✓	
	Appetite and food satisfaction			✓		✓		✓	
**Physical activity and function**									
	SPPB^d^			✓		✓		✓	
	Handgrip strength			✓		✓		✓	
	Physical activity record	✓		✓		✓		✓	
**Others**									
	Sociodemographic data and medical history	✓		✓					
	Knowledge, attitude, and practices	✓		✓					
	Medication log	✓		✓		✓		✓	
	Quality of life (WHOQOL-BREF^e^)			✓		✓		✓	
	Adverse events report					✓		✓	

^a^MAMC: midarm muscle circumference.

^b^nPCR: normalized protein catabolic ratio.

^c^MIS: malnutrition inflammation score.

^d^SPPB: Short Physical Performance Battery.

^e^WHOQOL-BREF: World Health Organization Quality of Life-BREF.

#### Anthropometric Data

Postdialysis weight, height, BMI, TSF, and mid–upper arm circumference will be measured using standard protocols. MAMC will be calculated as *MAMC=mid*–*upper arm circumference−(π×TSF)*. Body composition will be assessed using bioelectrical impedance analysis where available.

#### Biochemical Data

Laboratory parameters (renal, lipid, glucose, inflammation, dialysis adequacy, and protein intake) will be extracted from hospital records. hs-CRP will be analyzed externally using 10 mL fasting blood samples collected by trained staff.

#### Malnutrition Inflammation Score

Nutritional and inflammatory status will be assessed using the MIS (range 0-30). This tool has been locally validated, with a score of <5 indicating normal status and ≥5 indicating malnutrition [5].

#### Dietary Assessment and Compliance Toward Diet Regime

Participants will complete a 3-day food diary monthly (2 weekdays and 1 weekend). At the first clinic visit, participants will receive training on how to accurately record only foods and beverages consumed using household measurements and a colored food album to assist with portion size estimation. Dietary intake data will then be analyzed using Nutritionist Pro (version 5.1.0; Axxya Systems [22]) using information from the Nutrient Composition of Malaysian Foods and Singapore Food Composition Book (Ministry of Health Singapore [23,24]).

Dietary adherence will be evaluated using a binary compliance scoring system, as detailed in Tables 2 and 3. Although arbitrarily set, the scoring categories were informed by clinical relevance, current dietary guidelines (medical nutrition therapy and Kidney Disease Outcomes Quality Initiative), and prior literature on compliance assessment in chronic disease populations [7,21,25].

**Table 2 table2:** Dietary compliance scoring system (scored per day).

Category				Scoring criteria^a^		
				Score=0		Score=1
**Meal composition**						
	Meal frequency		Skipped ≥1 main meal/day		Consumed 3-4 main meals/day, without skipping	
	**Protein source**					
		Control	<50% protein intake from HBV^b^ animal-based sources		≥50% protein intake from HBV animal-based sources	
		Intervention	<2/3 or 3/4 meals are plant-based food sources		≥2/3 or 3/4 meals are plant-based food sources	
**Nutrient intake**						
	Total energy intake		Deviation of >+20% or −20% of target energy prescription		Within +20% or −20% of target energy prescription	
	Total protein intake		Deviation of >+20% or −20% of target protein prescription		Within +20% or −20% of target protein prescription	
	Total sodium intake		Outside 2000-3000 mg/day		Within 2000-3000 mg/day	
	Total potassium intake		Outside 2000-3000 mg/day		Within 2000-3000 mg/day	
	Total phosphate intake		Outside 0.8-1.0 g/day		Within 0.8-1.0 g/day	

^a^Total scores=0-7 (each daily dietary record is scored out of 7 points).

^b^HBV: high biological value.

**Table 3 table3:** Diet compliance score classification.

	Per day (1-day)	Per monthly review (3-day)	Per monthly review (3-day)
Maximum score	7	21	21
Total score	—^a^	<10.5/21 (<50%)	≥10.5/21 (≥50%)
Classification	—	Poor compliance	Adequate compliance

^a^Not applicable.

Each daily dietary record is scored out of a maximum of 7 points. A “1-day” record refers to a single 24-hour dietary record, whereas a “3-day” record represents the aggregation of three separate daily dietary records collected from participants. The total score for each 3-day dietary assessment therefore ranges from 0 to 21 points. Total scores are calculated by summing the scores from each daily record. A total score of ≥50% (≥10.5/21) indicates adequate dietary compliance, whereas scores <50% indicate poor compliance. To ensure feasibility and acceptability, the dietary compliance scoring system will be pilot tested with participants during the first 2 weeks of the study period.

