### Research Objectives

The primary objective is to determine the effect of a plant-focused dietary intervention on changes in serum albumin from baseline to 6 months compared with standard-of-care renal diet in malnourished patients undergoing PD.

The secondary objectives are (1) to determine the effect of a plant-focused dietary intervention on changes in anthropometric measurements (BMI, TSF, and MAMC), biochemical and inflammatory markers (lipid profile, hs-CRP, and renal parameters), dietary adequacy and nutrient intake, MIS scores, physical function and muscle strength, QOL, appetite scores, and dialysis adequacy from baseline to 6 months compared with standard-of-care renal diet in malnourished patients undergoing PD and (2) to determine the baseline nutritional status of malnourished patients undergoing PD, including their knowledge, attitude, and practices of renal diet intake, as well as sociodemographic characteristics and medical history.

Exploratory objectives are to assess adherence to a plant-focused dietary intervention over the 6-month period and to evaluate retention rates over 6 months of intervention.

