#### Intervention Group vs Control Group

The control group will follow a standard renal diet and be encouraged to maintain their usual dietary and physical activity patterns, with guidance to ensure that at least 50% of their total protein intake comes from high biological value animal-based sources. The standard renal diet was chosen as comparator as it reflects the current clinical practice. In contrast, the intervention group will follow a plant-focused dietary pattern that emphasizes plant-based foods, such as fruits, vegetables, legumes, whole grains, nuts, seeds, and plant oils, with minimal reliance on animal-based products. Participants in the intervention group will be required to consume plant-focused meals for most of their daily meals. For example, those consuming 3 meals per day must ensure that at least 2 out of the 3 meals are plant based, while those consuming 4 meals per day must ensure that at least 3 out of the 4 meals are plant based. The remaining meal or snack may include either plant- or animal-based foods to support flexibility and adherence.

Participants in both groups will receive individualized dietary counseling at each data collection point (baseline, 3 months, and 6 months). In addition, participants are also provided with educational pamphlets and 14-day structured meal plans that incorporate natural food sources and culturally appropriate meal choices. Meal plans for both groups are developed in accordance with the Malaysian Medical Nutrition Therapy Guidelines for Chronic Kidney Disease and the Kidney Disease Outcomes Quality Initiative Clinical Practice Guidelines for Nutrition in CKD [7,21]. Throughout the study, participants will continue to receive standard medical care, with no specific concomitant care prohibited.

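### The adequate/poor compliance class does not measure adherence to the plant-focused diet: the only arm-specific item carries 3 of 21 points and need not be met

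*Protocol article*

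**What the plan says.** Research Objectives lists adherence as exploratory: "Exploratory objectives are to assess adherence to a plant-focused dietary intervention over the 6-month period". The section on dietary assessment and compliance names one instrument for it, the binary score in Tables 2 and 3, and says openly that the scoring categories were set arbitrarily, though informed by guidelines and literature.

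Table 2 has seven equally weighted 0/1 items per diary day. Meal frequency, energy, protein, sodium, potassium and phosphate are worded identically for both arms, for example "Within +20% or −20% of target energy prescription". Protein source is the only item that differs. The control arm scores a point for "≥50% protein intake from HBV animal-based sources"; the intervention arm scores a point for "≥2/3 or 3/4 meals are plant-based food sources".

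The days are then added: "The total score for each 3-day dietary assessment therefore ranges from 0 to 21 points". The class follows from the sum alone: "A total score of ≥50% (≥10.5/21) indicates adequate dietary compliance, whereas scores <50% indicate poor compliance".

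The requirement that defines the experimental arm is in Intervention Group vs Control Group: "Participants in the intervention group will be required to consume plant-focused meals for most of their daily meals". Participant Withdrawal and Dropouts uses the same score: falling below 50% at three monthly reviews in a row is its second criterion. Table 4 plans descriptive statistics and a chi-square test for adherence, without saying whether the total, the class or single items are analysed.

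**The concern.** The objective asks whether participants followed the plant-focused diet. The named instrument mostly measures something else, namely whether they ate regularly and kept within nutrient ranges that apply equally to both arms. The arm-specific item is a seventh of the score and is not a condition for being classed as adequate.

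The class can therefore rank a participant who ignored the plant-meal rule above one who followed it every day. A compliance rate built on it says little about how far the two arms' diets differed, which is what a reader of the albumin result will look for in an adherence table. The class also helps decide who leaves the trial, so its errors are not confined to an exploratory table.

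**Working it through.** **Inputs.** Seven items per day, three days per review, a cut-off of 10.5 (Tables 2 and 3). One arm-specific item and six common items per day (Table 2).

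**The plan's own figures.** 7 × 3 = 21 points, and 50% of 21 = 10.5. Both reproduce. Scores are whole numbers, so the working cut-off is 11.

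**Weight of the arm-specific item.** 1 × 3 = 3 of 21 points, 3/21 = 14.3%. The common items hold 6 × 3 = 18 points.

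**No plant-based meals on any of three days.**
- Maximum score: 18/21 = 85.7%, adequate.
- Any 11 of the 18 common points are enough: 11/18 = 61%.

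**Plant-meal rule met on all three days.**
- No meals skipped, all five nutrient items out of range: (1 + 1) × 3 = 6, and 6/21 = 28.6%, poor.
- The class stays poor with up to 7 of the 18 common points: (3 + 7)/21 = 10/21 = 47.6%.

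**How often this might occur.** The documents give no pass rates. As an assumption, let each common item be passed independently with probability p. With no plant days the class is adequate if at least 11 of 18 common items are passed. With three plant days, at least 8 of 18 are needed. Binomial tail probabilities of being classed as adequate:

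| p | no plant days | plant rule met on all 3 days |
|---|---|---|
| 0.5 | 0.24 | 0.76 |
| 0.6 | 0.56 | 0.94 |
| 0.7 | 0.86 | 0.99 |
| 0.8 | 0.98 | 1.00 |

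At p = 0.7 or above, the class hardly separates a participant who never followed the plant rule from one who always did. The 18/21 and 6/21 results need no such assumption.

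**Can one menu satisfy both protein-source criteria?** One criterion is a share of protein, the other a count of meals. Take three meals, two of them plant based, with plant protein b in total and high-biological-value animal protein a in the third. The meal count is 2/3, so the intervention criterion is met. The control criterion is met when a/(a + b) ≥ 0.5, that is, when a ≥ b. With assumed figures of b = 12 + 12 = 24 g:
- a = 30 g gives 30/54 = 55.6%, and both criteria are met.
- a = 24 g gives 24/48 = 50%, and both are just met.
- a = 20 g gives 20/44 = 45.5%, and only the intervention criterion is met.

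Overlap is therefore possible. The documents do not show how common it would be.

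**The case against.** The strongest reply is that the six common items belong to the prescription. Both diets are tailored to individual nutrient needs and both sets of meal plans follow the same renal guidelines, so a score covering energy, protein and minerals does measure adherence to the whole prescription. A participant who met the plant-meal rule while eating far too little would not be following the plan. This stands, and it is a reason to keep those items. It does not make their sum a measure of adherence to the plant-focused diet.

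A reader might infer that the adherence objective cannot be answered at all. The documents do not support that. The protein-source item is scored on every diary day, and Table 4 does not confine the analysis to the total or the class, so the answer can be drawn from planned data.

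A reader might also infer that a null albumin result could not be told apart from a lack of dietary contrast. That goes too far as well. Food records are taken at each assessment, nutrient intake is computed from the diaries, and dietary intake is a secondary outcome compared between arms.

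Two further points are fair. The overlapping-menu example uses assumed protein values, and the intervention text also asks for little dependence on animal foods, although it lets the remaining meal be animal based. And how an incomplete diary is scored may be settled in the full protocol, so no criticism is made of it here.

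Finally, the objective is exploratory, and the primary analysis is by intention to treat and does not use the score. Its one route to the primary result is withdrawal: if withdrawal ends albumin measurement, last observation carried forward would put an earlier value in place of the month-6 one.

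**Conclusion.** The point holds for the total-score class. As fixed in Tables 2 and 3, that class does not measure adherence to the plant-focused diet: 3 of 21 points depend on the assigned diet, 18/21 (86%) is attainable with no plant-based meals, and 6/21 (29%) is possible with the plant-meal rule met every day. These figures follow from the scoring table alone. The probabilities by pass rate and the overlapping menu rest on stated assumptions and only illustrate.

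The weights, the cut-off and the classification are all stated, so this is a measure fixed badly and not detail left for another document. It should be changed, but it does not threaten the primary analysis directly.

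The compliance scoring, the intervention requirement and the second withdrawal criterion do not fit together: a participant who meets the plant-meal rule could satisfy that criterion while one eating no plant-based meals does not. These sections must be reconciled. This review does not say which rule should apply.

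**What to change.** 1. Report the protein-source item on its own, as days met divided by days recorded, by arm and monthly review. Name this as the measure of adherence to the assigned diet.
2. From the same diaries, score both quantities in both arms: the share of meals that are plant based, and the percentage of protein from high-biological-value animal sources. Report the between-arm separation at each review. This deals with the difference in units and shows any overlap directly.
3. Keep the other six items as a separate nutrient-target score, reported beside the first and not added to it.
4. Reconcile Participant Withdrawal and Dropouts, Intervention Group vs Control Group, and Tables 2 and 3 on what the compliance class is meant to represent.

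Reweighting within one total is a poor substitute. With weight w on protein source, the common items alone reach 6/(6 + w) of the maximum. That is still 50% at w = 6 and falls below the cut-off only when w exceeds 6 (6/13 = 46% at w = 7).

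Steps 1 to 3 need no new data, only some rescoring of three-day diaries already collected each month. With 9 participants recruited at submission, this can be specified now. The downside is that reported adherence may look lower than under the seven-item total. Step 4 may cost more than rescoring if it leads to a change in the protocol text after recruitment has begun.

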#### Appetite and Food Satisfaction Assessment

Appetite will be assessed using the validated Appetite and Food Satisfaction Questionnaire, which scores appetite and satisfaction from 0 to 18 (lower=better appetite) [26].

#### Quality of Life

QOL will be measured using the World Health Organization Quality of Life-BREF, comprising 26 items across 4 domains (physical, psychological, social, and environmental) [27]. Scores are converted to a 0 to 100 scale, with higher scores reflecting better QOL.

#### Physical Activity and Function

Physical activity will be measured using the short form of the International Physical Activity Questionnaire [28]. Results will be expressed in Metabolic Equivalent of Task minutes per week. Physical function will be assessed using the Short Physical Performance Battery, a well-established, standardized instrument that has been extensively used and validated in dialysis populations worldwide, with higher total scores indicating better physical function [29,30]. Handgrip strength will be measured using a Jamar dynamometer, with the mean of 3 consistent trials recorded.

#### Knowledge, Attitude, and Practices on Renal Diet

A validated 34-item questionnaire will assess dietary knowledge (12 items), attitude (7 items), and practice (15 items) [31]. Higher scores reflect better understanding and adherence to renal diet principles.

#### Sociodemographic and Medical History

Sociodemographic and medical history are collected via a structured interview guided by a general questionnaire covering demographic data, socioeconomic status, medical and dialysis history, medications, physical activity, and allergies.

### Statistical Analysis

Statistical methods are detailed in Table 4. Data will be analyzed using SPSS (version 28; IBM Corp). Normality of continuous data will be tested using the Kolmogorov-Smirnov test.

**Table 4 table4:** Summary of the statistical analysis.

Study outcomes	Variables	Statistical analysis
Primary or main outcome	Serum albumin	GLM^a^-repeated measures (time×group interaction)
Secondary outcomes	Anthropometric data Biochemical data Dietary adequacy Physical function Quality of life Appetite and food satisfaction Dialysis adequacy	GLM-repeated measures (time×group interaction)
Exploratory or feasibility outcomes	Dietary adherence or compliance Retention rate	Descriptive statistics and chi-square test

^a^GLM: generalized linear model.

The primary analysis will evaluate changes in serum albumin from baseline to 3 and 6 months between intervention and control groups. A generalized linear model for repeated measures will be used to assess time, group, and interaction effects. Analyses will follow the intention-to-treat principle, with missing data handled using the last observation carried forward method. Adjustment for potential confounders such as age, sex, dialysis duration, and baseline nutritional status will be performed using multivariable models. Bonferroni correction will be applied for multiple comparisons. Secondary outcomes, including anthropometric, biochemical, dietary, MIS, physical function, QOL, appetite, and dialysis adequacy parameters, will be analyzed using similar repeated-measures approaches. Statistical significance will be set at *P*<.05.

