#### Sample Size

The sample size was calculated using the standard formula for comparing 2 independent means in a parallel-group design using several assumptions.

On the basis of previous studies in dialysis populations, an estimated SD of 5 g/L was used to account for heterogeneity and to avoid underestimation of sample size. Notably, studies by Kalantar-Zadeh et al [17] and Rambod et al [18] reported serum albumin SDs ranging from 1.9 to 4.4 g/L, while a study by Limwannata et al [19] reported an SD of 5.0 g/L.

A clinically meaningful difference (δ) of 3 g/L (0.3 g/dL) was selected as it is consistent with differences in serum albumin levels observed across dialysis populations in previous studies. For instance, variations of 0.3 to 0.4 g/dL are observed between cohorts reported in studies by Rambod et al [18] and Limwannata et al [19]. Additionally, serum albumin is a well-established predictor of morbidity and mortality in patients undergoing dialysis, and even modest changes are considered clinically relevant in reflecting improvements in nutritional status [17].

Using the formula mentioned below, a 2-sided significance level of.05 (Zα/2=1.96) and 80% power (Zβ=0.84) were used to calculate the sample size. As a result, a minimum of 44 participants per group was required. After accounting for an anticipated 10% dropout rate, the sample size was rounded up to 50 participants for each group, with a total sample size of 100 participants. As repeated measurements will be conducted at baseline, 3 months, and 6 months, the calculated sample size is considered conservative.

The sample size was calculated using the standard formula for comparing 2 independent means in a parallel-group design, as shown below:

[figure not shown]

Where n is the sample size per group, Zα*/*2 is the standard normal deviate for a 2-sided significance level (1.96 for *α*=.05), Zβ is the standard normal deviate for power (0.84 for 80% power), σ is the SD, and δ is the expected difference between groups.

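### Dietary adherence is scored 0 to 21 each month, but the only classification defined is a cut at 10.5 and the only test named is chi-square; modelling the monthly score would use the data better

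*Protocol article*

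**What the plan says.** Participants keep a three-day food diary every month. Table 2 scores each day on seven yes/no items, and the three days are summed to a total out of 21. The section Dietary Assessment and Compliance Toward Diet Regime then splits the total in two: "A total score of ≥50% (≥10.5/21) indicates adequate dietary compliance, whereas scores <50% indicate poor compliance". It says of its scoring: "Although arbitrarily set, the scoring categories were informed by clinical relevance", and goes on to cite dietary guidelines and earlier literature on compliance.

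Under Research Objectives the article states: "Exploratory objectives are to assess adherence to a plant-focused dietary intervention over the 6-month period". Table 4 lists the exploratory or feasibility outcomes as "Dietary adherence or compliance Retention rate" and gives both the same methods: "Descriptive statistics and chi-square test". The primary and secondary outcomes, including appetite, quality of life and physical function, are analysed on their own scales with repeated-measures models.

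**The concern.** A score with 22 possible values, recorded every month, appears to be reduced to yes or no before it is tested. Three things follow.

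- Someone scoring 11 counts the same as someone scoring 21, while 10 and 11 fall in different classes.
- An ordinary chi-square test takes one independent value per person. It can be run at one month, or on one summary per person, but it cannot use the monthly series that an objective covering six months calls for.
- A cut at 50% is least informative when most people are above it. Dietitian-led counseling and the closer early monitoring aim for exactly that. The section Participant Withdrawal and Dropouts also lists repeated scores below 50% as a withdrawal criterion, so later months may contain few participants classed as poor.

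At stake is the precision of an exploratory comparison: a moderate difference in adherence between arms would be harder to see than the data allow.

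**Working it through.** **The plan's own figure.** The article gives no power or sample size for adherence, only for serum albumin: "a 2-sided significance level of.05 (Zα/2=1.96) and 80% power (Zβ=0.84) were used to calculate the sample size"; "an estimated SD of 5 g/L was used to account for heterogeneity"; "A clinically meaningful difference (δ) of 3 g/L (0.3 g/dL) was selected". So n = 2 × (1.96 + 0.84)² × 5² / 3² = 43.6, rounded up to 44 per arm as stated. Allowing for 10% dropout, 44 / 0.90 = 48.9, so 49, which the article rounds up to 50. This reproduces. It also fixes the group sizes used below: 50 per arm as randomized and 50 × 0.90 = 45 after dropout.

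**Assumptions.** The article states no mean, SD, adequate share or between-arm difference for the adherence score. Assumed here:

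- an approximately normal score with SD 3 or 4 points;
- a higher-arm mean from 10.5 plus half the difference (arms symmetric about the cut) up to 15;
- a between-arm difference d of 0.3, 0.5 or 0.6 SD;
- two-sided alpha 0.05 and one time point.

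**Formulas.**

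- Score: two-sample t test, noncentral t with 2n − 2 degrees of freedom and noncentrality d × √(n/2).
- Cut score: adequate share in each arm = Φ((mean − 10.5)/SD), then exact binomial power of the uncorrected Pearson chi-square.

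**Worked case.** 45 per arm, means 14 and 12.5, SD 3.

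- d = 1.5/3 = 0.5, and noncentrality = 0.5 × √22.5 = 2.37. Power for the score is 65%.
- Adequate shares: Φ(3.5/3) = Φ(1.167) = 88% and Φ(2.0/3) = Φ(0.667) = 75%. Power of the chi-square is 37%.
- Loss: 65 − 37 = 28 points.
- A simulation with whole-number scores clipped to 0–21 (20,000 trials) gave 64.5% and 36.9%.

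**Across the assumed range.**

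| n per arm | Difference | Power, score | Power, chi-square | Loss (points) |
|---|---|---|---|---|
| 45 | 0.3 SD | 29% | 14–20% | 9–15 |
| 45 | 0.5 SD | 65% | 30–46% | 19–35 |
| 45 | 0.6 SD | 80% | 42–60% | 20–39 |
| 50 | 0.3 SD | 32% | 13–24% | 8–19 |
| 50 | 0.5 SD | 70% | 32–53% | 16–38 |
| 50 | 0.6 SD | 84% | 45–68% | 16–40 |

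**Sensitivity to the adequate share.** With normal-approximation formulas, 50 per arm and d = 0.6 (score power about 85%), the loss is about 19 points when the average adequate share is 50%, 24 at 70%, 31 at 80%, 46 at 90% and 58 at 95%. Over a wider grid (44 to 50 per arm, d from 0.3 to 0.8, adequate share 50% to 95%) it runs from about 9 to about 74 points.

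These figures cover a comparison of arms at a single time point. Decline in adherence over the months was not modelled.

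**The case against.** The strongest reply is that the article never says chi-square is applied to the adequate/poor split. The Table 4 cell is shared with retention, for which chi-square is the obvious test, and descriptive statistics could report the 0–21 score month by month. The objective speaks of adherence to the plant-focused diet and the table calls the outcome exploratory or feasibility, which can be read as a descriptive question within one arm. No power target is attached. This stands in part: the reading is an inference. But the row names no other test, and no adherence categories other than adequate and poor are defined, so it is the natural one.

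The 50% cut also has a use of its own, because the same threshold appears in the withdrawal criteria. That stands as a reason to report the proportion. It is not a reason to test only the proportion.

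Five of the seven items are nutrient intakes, and dietary adequacy is already a secondary outcome with a repeated-measures model. Part of the information will therefore be analysed elsewhere, though not the compliance score itself.

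Two stronger readings are tempting. A reader might infer that adherence will be used to decide whether a null albumin result reflects the diet or poor uptake. The article does not say so, and the total score would serve that purpose poorly: six of the seven items have the same criteria in both arms, and only the protein-source item differs by arm. A reader might also take 16 to 40 points as a fixed cost of this plan. It is not, since it rests on an assumed difference, SD and mean.

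**Conclusion.** The point holds as a low-priority improvement. On the natural reading of Table 4, testing adherence as adequate or poor discards information and leaves the monthly series unused, while comparable scales in the same plan are kept whole.

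Every setting checked shows a loss, but its size is conditional. It is about 8 to 19 points at 0.3 SD, where the uncut score itself has only about 29% to 32% power. It is about 16 to 40 points at 0.5 to 0.6 SD with the higher-arm mean no more than 15. At 0.6 SD it is larger still if about 90% or more of participants are adequate. None of the inputs on the score's distribution comes from the article.

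Adherence is exploratory, so neither the albumin analysis nor its sample size is affected.

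**What to change.** In Table 4, give dietary adherence its own row. Analyse the 0–21 score (or percent of maximum) at each monthly review by arm, with the repeated-measures approach already planned for the secondary outcomes, and report the mean difference with a 95% confidence interval. Keep the adequate/poor proportion as a descriptive summary, since the same 50% threshold appears among the withdrawal criteria. Keep chi-square for retention. Neither the threshold nor the withdrawal criteria need to change for this.

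The cost is a wording change and one extra model on diaries already being collected, with no new visits, data or participants. A small downside is that a mean score is less direct to communicate than a percentage classed as adequate, but that percentage is still reported. The article reports 9 participants recruited at submission, so a change made early would still come well before any outcome analysis.

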### Research Hypotheses

The first alternative hypothesis is as follows: the serum albumin level improved significantly among malnourished patients undergoing PD following a plant-focused diet compared to a standard-of-care renal diet after 6 months of intervention.

The second alternative hypothesis is that other nutritional outcomes, such as anthropometric measurements (BMI, TSF, and MAMC), biochemical and inflammatory marker (lipid profile, hs-CRP, and renal parameters), dietary intake, MIS scores, assessment of physical function, QOL, appetite, and retention rate in the trial, improved significantly among malnourished patients undergoing PD following the plant-focused diet in comparison to a standard-of-care renal diet after 6 months of intervention.

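### The primary test is a three-visit time-by-group interaction, not the 6-month albumin difference in the objective; it can be positive with no 6-month effect, and the stated 80% power does not carry over to it

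*Protocol article*

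**What the plan says.** The question is put at 6 months. In Research Objectives: "The primary objective is to determine the effect of a plant-focused dietary intervention on changes in serum albumin from baseline to 6 months". In Research Hypotheses, albumin is expected to be better "following a plant-focused diet compared to a standard-of-care renal diet after 6 months of intervention".

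The Sample Size section uses the formula for two independent means: difference 3 g/L, SD 5 g/L, two-sided alpha .05, 80% power. This gives 44 per group, raised to 50 for 10% dropout. The section names no visit and no within-patient correlation, and it adds: "As repeated measurements will be conducted at baseline, 3 months, and 6 months, the calculated sample size is considered conservative".

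The analysis is put differently. In Statistical Analysis: "The primary analysis will evaluate changes in serum albumin from baseline to 3 and 6 months between intervention and control groups". The Table 4 entry for serum albumin is "GLM^a^-repeated measures (time×group interaction". The text adds that time, group and interaction effects will be assessed, that significance is P<.05, and that "Bonferroni correction will be applied for multiple comparisons", without saying which comparisons this covers. No between-group contrast at month 6 is named as the primary test.

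**The concern.** With assessments at months 0, 3 and 6, the time-by-group interaction asks whether the difference between the arms varies in any way across three visits. The objective asks about one visit. The two can disagree in both directions. A difference at month 3 that has vanished by month 6 can make the primary test significant although the answer to the objective is null. A real 6-month effect is tested on 2 degrees of freedom, with power that depends on its shape over time and on the within-patient correlation.

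The sample size is for a comparison on 1 degree of freedom that is not the planned primary test. Its 80%, and the remark that repeated measurement makes it conservative, therefore do not describe that test.

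**Working it through.** **1. The plan's own figure.** n = 2(1.96 + 0.84)² × 5² / 3² = 2 × 7.84 × 25 / 9 = 43.6, so 44 per group. 44 / 0.9 = 48.9, rounded up to 50. Both figures reproduce. Power at 44 per group is 80% by the normal formula (79.5% by the exact t test).

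**2. Inputs for the interaction test.** From the protocol: visits at months 0, 3 and 6, SD 5 g/L, target difference 3 g/L, 44 evaluable per group, alpha .05. Assumed, because the documents give neither: within-patient correlation ρ of 0.3, 0.5 or 0.7 with compound symmetry, and the shape of the between-arm difference d over the visits.

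**3. Formula.** Noncentrality λ = (n/2) × Σ(d − d̄)² / [σ²(1 − ρ)], referred to F with 2 and 2(2n − 2) = 172 degrees of freedom. The multivariate version of the test agrees within 1 percentage point.

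Values of Σ(d − d̄)²:
- d = (0, 1.5, 3): mean 1.5, sum 2.25 + 0 + 2.25 = 4.5
- d = (0, 3, 3): mean 2, sum 4 + 1 + 1 = 6
- d = (0, 3, 0): mean 1, sum 1 + 4 + 1 = 6
- d = (0, 1.5, 0): mean 0.5, sum 0.25 + 1 + 0.25 = 1.5

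Example: (0, 1.5, 3) at ρ = 0.5 gives λ = 22 × 4.5 / 12.5 = 7.92 and power 70%.

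**4. Results, 44 per group.**

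| Difference at months 0, 3, 6 (g/L) | Test | ρ 0.3 | ρ 0.5 | ρ 0.7 |
|---|---|---|---|---|
| 0, 1.5, 3 | interaction | 55% | 70% | 91% |
| 0, 3, 3 | interaction | 68% | 83% | 97% |
| 0, 3, 0 (none at month 6) | interaction | 68% | 83% | 97% |
| 0, 1.5, 0 (none at month 6) | interaction | 21% | 28% | 44% |
| 0 at month 6, any value at month 3 | month-6 contrast | 5% | 5% | 5% |
| 3 at month 6 | change from baseline to month 6 | 65% | 79% | 95% |
| 3 at month 6 | month-6 albumin adjusted for baseline | 83% | 90% | 97% |

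The last two rows use SD 5√(2(1 − ρ)) for the change and 5√(1 − ρ²) for the adjusted value.

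**5. Reading the table.** The second and third rows are identical because Σ(d − d̄)² is 6 in both. Under these assumptions the interaction test cannot tell a sustained effect from one that has disappeared by month 6. A 10,000-trial simulation at ρ = 0.5 agreed: 82% significant for (0, 3, 0), 70% for (0, 1.5, 3) and 83% for (0, 3, 3).

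**6. Sensitivity.** With linear build-up the interaction reaches 80% at ρ of about 0.6. With all 50 per group it has about 60%, 76% and 94% at ρ 0.3, 0.5 and 0.7. Under first-order autoregressive correlation, linear build-up at 44 per group gives 43% to 84% over ρ 0.3 to 0.8.

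**The case against.** **Power is not uniformly low.** If the full 3 g/L is present at both follow-up visits, or the correlation is about 0.6 or more, the interaction meets or exceeds 80%. SD 5 g/L is also the top of the range that the Sample Size section quotes; at 4.4 g/L, linear build-up with ρ = 0.5 gives 82%. This stands. The 80% is unsupported for the planned test, but the trial is not shown to be underpowered.

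**The 83% is an extreme case.** It needs the full target effect at month 3 and none at month 6, although the diet continues throughout. That is fair; 1.5 g/L at month 3 only gives 28% at ρ = 0.5. Even so, this is well above 5%.

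**A month-6 comparison may be intended, and contrasts are often left to an analysis plan.** Possibly. But this article fixes a primary test in Table 4, and it is a different one from the objective.

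A reader might also infer three stronger points that the documents do not support:
- That the primary test runs at a smaller alpha. The significance level is .05 in both sections, and the Bonferroni sentence is neither tied to the interaction nor given a number of comparisons.
- That baseline albumin enters as both response and covariate. The text reads "Adjustment for potential confounders such as age, sex, dialysis duration, and baseline nutritional status will be performed using multivariable models"; it does not say that baseline nutritional status means albumin, and the protocol also assesses nutritional status with the malnutrition inflammation score.
- That the main effect of group, which averages in baseline, decides the trial. Table 4 names the interaction.

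**Conclusion.** The point holds. The objective and hypothesis are about the between-arm difference in albumin change at 6 months, while the stated primary test is an omnibus interaction over three visits. That mismatch is on the page and needs no assumption. That the sample size refers to month 6 is an inference from the objective, because the Sample Size section names no visit.

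The size of the problem rests on assumed correlation and effect shape. Over ρ 0.3 to 0.7 with compound symmetry and 44 per group, an effect confined to month 3 makes the primary test significant in 21% to 44% of trials (1.5 g/L) or 68% to 97% (3 g/L). Power for a true 3 g/L effect at month 6 runs from 55% to 97%, so it may lie below or above the stated 80%. Without a stated correlation, repeated measurement is no ground for calling the size conservative for this test.

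**What to change.** In Statistical Analysis and Table 4, name one primary estimate: the between-arm difference in serum albumin at month 6, adjusted for baseline albumin, with its 95% CI, tested at two-sided alpha .05. It can come from an analysis of covariance at month 6, or from the month-6 contrast of a repeated-measures model with baseline albumin as a covariate. As a single test it needs no Bonferroni adjustment.

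Make the 3-month contrast and the time-by-group interaction secondary. In Sample Size, state that the 3 g/L refers to month 6, and replace the sentence on conservatism with the power of the month-6 contrast over a stated range of correlations. At 44 per group, the baseline-adjusted contrast has about 83%, 90% and 97% for ρ 0.3, 0.5 and 0.7 under the assumptions above, so the planned size would then be adequate.

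The cost is wording only: same visits, data and 100 participants. With 9 participants recruited at submission and no interim analysis planned, the change can be dated well before outcomes are analysed.
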